## Abstract

**Background:**

Perianal abscesses are common anorectal conditions that often necessitate surgical intervention. Accurate preoperative assessment is crucial for effective treatment and reducing recurrence rates. Diffusion tensor imaging (DTI) is a valuable method for visualizing the degree of infection and infiltration, the extent of abscess formation, and the relationship between perianal abscess erosion. However, there is currently a lack of specific studies focusing on perianal abscesses.

**Objective:**

The objective of this study is to investigate the diagnostic utility of DTI in the preoperative assessment of perianal abscesses. By enhancing the precision of preoperative evaluation, we aim to minimize damage to the anal sphincter, reduce the recurrence rate, and improve the prognosis and quality of life for patients.

**Methods:**

This study adopts a randomized, prospective, single-blind design. Ninety participants are being randomized into 2 groups: a DTI group and a conventional magnetic resonance imaging group. A structured report is being completed based on imaging of the perianal abscesses in terms of location, number, specific pus cavity alignment, thickness, and relationship to the surrounding muscles. In addition, the patient condition is being assessed, and corresponding surgical treatment is being performed. If the patient’s blood routine shows infection, cefuroxime sodium combined with metronidazole is being administered intravenously as an anti-infective therapy. Postoperatively, the primary variable is being assessed for recurrence rate at 6 months, and the secondary variables, including postoperative pain scores on days 3 and 7, peripheral blood inflammatory factors, and assessment of anal function, are being evaluated. Normally distributed continuous data will be presented as mean (SD) and analyzed using independent or paired *t* tests. Non-normally continuous data will be analyzed with rank-sum tests. Categorical data will be expressed as frequency (%) and compared using a chi-square test or appropriate nonparametric tests. Ordinal data will be analyzed using the Ridit test. A *P* value <.05 will be considered statistically significant.

**Results:**

This study is funded by Science and Technology Commission of Shanghai Municipality Science and Technology Program (grant 23Y11920800). Patient recruitment was initiated in April 2025. As of January 2026, 37 participants have been enrolled, and data collection is scheduled to be completed in October 2026.

**Conclusions:**

DTI technique can be used to gain a deeper understanding of the relationship between internal orifice, the degree of infected infiltration, the extent of the abscess, and the involvement of the perianal tissues and muscles in patients with perianal abscess. Deep pelvic floor DTI reveals the complex 3D structure of the pelvic floor in perianal abscesses through structured reports, which may provide new insights into the diagnosis of perianal abscesses.

## Introduction

### Clinical Background and Diagnostic Challenges

Perianal abscesses are acute suppurative infections caused by obstruction of the anal gland opening and bacterial infection in the perianal tissues or spaces. They are among the most common anorectal diseases [1], particularly affecting young adults aged 20 to 40 years, with a higher prevalence in males than females [2]. Between 30% and 70% of patients with abscesses are often accompanied by anal fistula, while among patients without fistulas, the probability of developing an anal fistula is approximately 30% to 50% within months to years after abscess drainage [3]. Reducing recurrence rate and fistula rate of perianal abscesses remains a significant challenge. The recurrence rate after surgical intervention remains substantial, underscoring the need for improved diagnostic and therapeutic strategies [4].

The initial diagnosis of perianal abscesses is often based on clinical symptoms and anal palpation. However, this approach has limitations in dealing with multiple, high-grade perianal abscesses. In such cases, preoperative imaging, particularly magnetic resonance imaging (MRI), plays a pivotal role in accurate diagnosis and treatment [5,6]. MRI has a sensitivity of 96% and specificity of 97% for diagnosing abscesses [7]. Accurate assessment of the location, range, and depth of the abscess using MRI can help health care professionals develop more reasonable and effective surgical plans, including selecting the appropriate incision location, accurately positioning the internal opening, and employing the correct drainage method. This comprehensive approach aims to remove the infection as thoroughly as possible, reduce the risk of recurrence and fistula rate, and protect the anal function and quality of life of patients [8].

Diffusion-weighted imaging (DWI) is a variant of conventional MRI based on different rates of water diffusion in different tissues, offering unparalleled sensitivity to water motion within tissue structures [9,10]. Some studies have demonstrated the valuable role of DWI in the diagnosis and differential diagnosis of anal fistula and perianal abscess [11-13]. DWI exhibits high specificity in distinguishing abscesses from inflammatory masses, surpassing traditional MRI [12].

Diffusion tensor imaging (DTI) extends the principles of DWI by modeling water diffusion as a 3D tensor, thereby quantifying both the magnitude and directionality (anisotropy) of diffusion within tissues [14]. Originally developed for neural tractography, DTI has shown promise in musculoskeletal and pelvic floor imaging by revealing microstructural integrity and architectural disruption [15]. A pivotal study by Wang et al [16] demonstrated the feasibility of DTI in evaluating perianal fistula, suggesting that parameters such as fractional anisotropy (FA) and apparent diffusion coefficient could reflect tissue characteristics relevant to surgical planning. However, while this and other emerging studies hint at DTI’s potential, the existing literature remains strikingly sparse regarding its specific application to perianal abscesses. Current evidence is largely extrapolated from fistula research or limited to technical feasibility reports. Critical gaps persist: there is a lack of standardized, quantitative DTI protocols for preoperatively mapping abscess extent, infection infiltration, and precise involvement of the anal sphincter complex and levator ani muscle. Moreover, it remains unclear whether the microstructural metrics provided by DTI correlate with surgical outcomes, such as recurrence rates or postoperative anal function.

### Objectives of the Study

The primary goal of this study is to use DTI to delineate the relationship between the internal opening, the degree of infection and infiltration, the extent of the abscess, and the erosion of perianal tissues and muscles in patients with perianal abscesses. This approach aims to develop an accurate imaging evaluation method for diagnosing the disease, explore the application value of DTI in the diagnosis of perianal abscesses, and improve the accuracy of preoperative evaluation, as well as reduce the damage to the anal sphincter. Ultimately, these efforts aim to reduce the recurrence rate and improve the prognosis and quality of life for patients.

## Methods

### Study Design

This study adopts a randomized, controlled, single-blind design to compare the structural characteristics of perianal abscesses and the recurrence rate at 6 months after surgery between the DTI group and the conventional MRI group. Figure 1 illustrates the study flowchart. The schedule of enrollment, interventions, and assessments, in accordance with the SPIRIT (Standard Protocol Items Recommendations for Interventional Trials) guidelines, is summarized in Table 1.

**Figure 1. F1:**
[figure not shown]
Flowchart of the trial. DTI: diffusion tensor imaging; IL-1β: interleukin-1β; IL-6: interleukin-6; MRI: magnetic resonance imaging; TNF-α: tumor necrosis factor-α.

**Table 1. T1:** The Standard Protocol Items Recommendations for Interventional Trials (SPIRIT) schedule table.

	Study period						
	Enrollment	Allocation	Postallocation				Close-out
Timepoint	–t_1_	0	t_1_ (preoperation)	t_2_ (immediately after operation)	t_3_ (the third day after the operation)	t_4_ (the seventh day after the operation)	t_5_ (6 mo after the operation)
Enrollment							
Eligibility screen	✓						
Informed consent	✓						
Allocation		✓					
Interventions							
Diffusion tensor imaging			✓				
Magnetic resonance imaging			✓				
Assessments							
Baseline variables: demographic data, vital signs testing, safety observation indicators			✓				
Recurrence rate							✓
Structured report				✓			
Postoperative pain score					✓	✓	
Detection of inflammatory factors			✓		✓		
Assessment of anal function			✓				✓

### Randomization

In this study, 90 patients with perianal abscess are sequentially numbered from 1 to 90 in order of enrollment. SPSS statistical software is used to generate 90 random 3-digit numbers, which are then sorted in ascending order. The first 45 numbers are assigned to the experimental group, and the remaining 45 to the control group. To implement allocation concealment, the randomization results are sealed in opaque, sequentially numbered envelopes by an independent research coordinator who is not involved in participant recruitment, clinical assessment, or data analysis. Once a patient meets the eligibility criteria and provides written informed consent, the independent coordinator opens the corresponding envelope according to the patient’s number and informs the radiology technician of the group assignment so that the appropriate MRI scanning protocol can be performed. The surgeon then reviews the imaging report generated based on this group assignment before surgery and formulates the surgical plan accordingly.

### Blinding

This study adopts a single-blind design in which participants remain unaware of their group assignments. Surgeons are necessarily unblinded due to the preoperative review of imaging reports. To minimize detection bias, all postoperative outcome assessments, including the evaluation of recurrence, pain scoring, anal function measurement, and inflammatory marker testing, are performed by independent assessors who remain blinded to group allocation throughout the trial.

### Sample Size Calculation

The sample size was calculated based on data from a preliminary pilot study involving 20 patients with perianal abscesses (10 in each preliminary subgroup). Previous studies have reported an overall postoperative recurrence rate for perianal abscess of approximately 11.7% [17]. In the pilot study, the 6-month postoperative recurrence rate was 15% among patients who underwent conventional MRI–guided surgical treatment, while the recurrence rate was 5% in those who received preoperative DTI assessment combined with targeted surgical intervention. Using a 2-sided α level of .05 and a β level of .20, the sample size for the intervention (DTI group) and control (conventional MRI group) was estimated using Power Analysis and Sample Size software (version 11), resulting in N1=N2=41. Considering a 10% potential attrition rate during follow-up, the required sample size for each group was adjusted to 45 (41/0.9), leading to a total enrollment of 90 participants for the formal study.

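### The pilot recurrence rates of 15% and 5% cannot arise from 10 patients per subgroup, so either the rates or the stated denominators are wrong, and the article does not show which

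*Protocol article*

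**What the plan says.** All the relevant figures are in the protocol article, Methods, Sample Size Calculation.

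- Pilot size: a "preliminary pilot study involving 20 patients with perianal abscesses (10 in each preliminary subgroup").
- Control rate, introduced as a pilot result: "the 6-month postoperative recurrence rate was 15% among patients who underwent conventional MRI–guided surgical treatment".
- DTI rate, in the same sentence: "the recurrence rate was 5% in those who received preoperative DTI assessment combined with targeted surgical intervention".
- A literature figure, given separately: an "overall postoperative recurrence rate for perianal abscess of approximately 11.7" percent. It is not offered as the source of either group's rate.
- Design settings and result: "Using a 2-sided α level of .05 and a β level of .20", "resulting in N1=N2=41", then "the required sample size for each group was adjusted to 45 (41/0.9), leading to a total enrollment of 90 participants".

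The Primary Efficacy Outcome section defines recurrence as an event that a patient either has or does not have by 6 months, and the Statistical Plan analyses it by binary logistic regression. The article gives no pilot event counts anywhere, and no other pilot denominators.

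**The concern.** With 10 patients in a subgroup, the proportion with recurrence can only be 0%, 10%, 20% and so on. Neither 15% nor 5% is on that list, yet both the denominators and the rates are reported as facts about one pilot. At least one of those statements is therefore untrue as printed.

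The 10-point difference is the only effect size on which the trial is planned, and it is presented as something observed. If the rates are wrong, the planning effect is wrong. If the denominators are wrong, the amount of evidence behind it is misdescribed. If the rates were assumed, an assumption is being presented as data. A reader cannot judge the power of the trial without knowing which applies.

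**Working it through.** **1. Counts implied by the stated figures.** Inputs: 10 per subgroup, 15% and 5%.

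- Conventional MRI: 0.15 × 10 = 1.5 patients.
- DTI: 0.05 × 10 = 0.5 patients.

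Neither is a whole number.

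**2. Can rounding or lost patients rescue the rates?** I searched every fraction k/n with n up to 20 that rounds to the stated whole percentages. For 15%, only 2/13 (15.4%) and 3/20 qualify. For 5%, only 1/19 (5.3%) and 1/20 qualify. Nothing with n of 10 or fewer works: the nearest to 15% are 1/7 = 14.3% and 1/6 = 16.7%, and the smallest non-zero rate is 1/10 = 10%.

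**3. Can a time-to-event estimate rescue them?** In a Kaplan-Meier estimate from at most 10 patients at risk, the first event adds at least 1/10 = 10%, so 5% is out of reach. For 15%, a single event gives 1/n (14.3% or 16.7% at nearest) and two events give at least 1 − (9/10)(8/9) = 20%.

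**4. What would fit.** The rates are exactly 3/20 and 1/20. Three explanations are consistent with that:

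| Explanation | True rates | True pilot size |
|---|---|---|
| 20 per subgroup, denominators misreported | 15% v 5% | 40 |
| Events divided by the pilot total of 20 | 3/10 = 30% v 1/10 = 10% | 20 |
| Rates not taken from this pilot | not known | 20 |

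**5. The plan's own sample size.** The pooled normal approximation for two proportions, with p̄ = (p1 + p2)/2, is

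n = [1.960 √(2p̄(1−p̄)) + 0.8416 √(p1(1−p1) + p2(1−p2))]² / (p1 − p2)².

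For 15% v 5%, p̄ = 0.10 and the two terms are 0.8315 and 0.3521. So n = (1.1836/0.10)² = 140.1, or 141 per group. The stated 41 is not reproduced. Unpooled, arcsine and continuity-corrected two-sided versions give 138, 133 and 160. That mismatch is a separate error.

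**6. How much the choice of rates matters.** I used the same formula at two-sided alpha .05 and 80% power. Power at 41 per group is Φ{[(p1 − p2)√41 − 1.960√(2p̄(1−p̄))] / √(p1(1−p1) + p2(1−p2))}.

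| Rates (control v DTI) | n per group | Power at 41 per group |
|---|---|---|
| 15% v 5% (as stated) | 141 | 32% |
| 30% v 10% (3/10 v 1/10) | 62 | 62% |
| 20% v 10% (2/10 v 1/10) | 199 | 24% |
| 10% v 0% (1/10 v 0/10) | 74 | 55% |
| 20% v 0% (2/10 v 0/10) | 35 | 87% |

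The last three rows are the attainable results nearest the stated ones. The fourth such pair, 10% v 10%, leaves no effect to power.

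**7. How far 10 patients fix a rate.** Exact (Clopper-Pearson) 95% intervals:

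- 0/10: 0% to 30.8%
- 1/10: 0.3% to 44.5%
- 2/10: 2.5% to 55.6%
- 3/10: 6.7% to 65.2%

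**The case against.** The best defence is that this is a reporting slip in the rationale. It leaves randomisation, the endpoint definition and the primary analysis untouched, and the denominators may be the misprint, with 20 per subgroup and the rates correct. That is plausible, and the first part stands: nothing in the conduct of the trial changes. It does not remove the contradiction, because the pilot size would then be wrong in print. Article condensation and PDF extraction do not explain it either, since the conflicting figures are printed intact in one paragraph. Reading the subgroups as something other than the two imaging groups does not help: 3/20 with 1/20 needs 40 patients, and 2/13 with 1/19 needs 32, against a stated 20.

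Three stronger readings are tempting, and the article does not support them.

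- A reader might infer that the true rates are 30% and 10%, so that both are understated by a factor of 2. That is one explanation among several, and nothing in the text favours it.
- A reader might infer that any restated power or sample size keeping 15% v 5% must be wrong. It need not be: those rates may be correct with misreported denominators, or may be kept openly as planning assumptions.
- A reader might infer that correction must weaken the basis for the design. At 30% v 10% the difference doubles to 20 points and the required size falls from 141 to 62 per group, which is more favourable. At 20% v 10% it rises to 199.

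**Conclusion.** The contradiction is certain; its source is not. Given a per-patient yes/no outcome and 10 patients per subgroup, 15% and 5% are impossible, so either the rates or the denominators are wrong as written. The consequence depends on which. Over the scenarios above, the required size runs from 35 to 199 per group, and power at 41 evaluable per group from about 24% to about 87% (32% at the stated rates, 62% at 30% v 10%). These figures assume the pooled normal approximation without continuity correction. They show sensitivity to the unresolved inputs and do not measure the error itself.

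The failure of 41 per group to follow from 15% v 5% is a distinct problem, and its weight is not counted here. Correcting either one leaves the other in place.

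**What to change.** In the Sample Size Calculation section:

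1. Give the actual pilot event counts and denominators for each subgroup, with exact 95% confidence intervals, and correct whichever of the rates or denominators is wrong.
2. If 15% and 5% were assumed, label them as planning assumptions and remove the statement that the pilot observed them.
3. Restate the power of the planned 41 evaluable per group on the corrected or declared rates. Show a range, because 10 patients per subgroup barely constrain them; for example, about 32% at 15% v 5% and about 62% at 30% v 10%.

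The cost is a wording correction from pilot records that the investigators should hold, plus a short recalculation. It needs no extra enrolment and no change to procedures or analysis. The downside is that the stated power or the basis for the effect size may look less favourable, depending on which figure proves wrong.

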### Primary Efficacy Outcome

This study assesses the recurrence rate of perianal abscess as the primary endpoint, evaluated at 6 months (±7 d) after surgery. Recurrence is defined by the reappearance of clinical symptoms (eg, perianal pain, swelling, or purulent discharge) along with confirmation on a follow-up MRI scan—specifically the DTI sequence—of a new or persistent fluid collection suggestive of an abscess. For the purpose of this primary outcome, the presence of a newly developed anal fistula also constitutes a recurrence event. All assessments for recurrence are performed by 2 independent, experienced radiologists. These radiologists are blinded to the patient’s group allocation and baseline imaging findings. Any discrepancy between their assessments is resolved either by consensus or by a third senior radiologist.

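### The stated planning inputs (15% vs 5%, two-sided 5% level, 80% power) need about 133–160 patients per group, not 41; at those rates the trial has roughly one-third power

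*Protocol article*

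**What the plan says.** Everything needed to check the figure is in the protocol article, under Sample Size Calculation.

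- Error rates: "Using a 2-sided α level of .05 and a β level of .20".
- Control rate: "the 6-month postoperative recurrence rate was 15% among patients who underwent conventional" MRI-guided surgery.
- Intervention rate: "the recurrence rate was 5% in those who received preoperative DTI assessment".
- Source of both rates: a 20-patient pilot, "10 in each preliminary subgroup".
- Result: the size "was estimated using Power Analysis and Sample Size software (version 11), resulting in N1=N2=41", then raised to 45 per group (90 in total) for 10% attrition.

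Allocation is 1:1 (Randomization). The Statistical Plan analyses 6-month recurrence as a binary outcome by logistic regression, at two-sided P<.05. For this endpoint, the Primary Efficacy Outcome section adds that "the presence of a newly developed anal fistula also constitutes a recurrence event". The sample size section does not say whether the pilot used that definition.

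**The concern.** A fall from 15% to 5% is a 10-point difference between two small proportions. Detecting it with 80% power ordinarily takes well over 100 patients per arm, so 41 is implausible on sight. The inputs also look unsound: a group of 10 can only yield multiples of 10%, yet the pilot is credited with 15% and 5%.

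The Discussion makes lower 6-month recurrence the study hypothesis. If the true rates are those assumed, a non-significant result is more likely than a significant one. A published claim of 80% power would then invite readers to take that result as evidence that DTI does not help.

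**Working it through.** **Inputs** (all from Sample Size Calculation): p1 = 0.15, p2 = 0.05, difference 0.10, mean rate 0.10, z for two-sided .05 = 1.960, z for 80% power = 0.8416, equal groups.

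**Attempt to reproduce 41.** Required n per group:

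- Unpooled variance: (1.960 + 0.8416)² × (0.15×0.85 + 0.05×0.95) / 0.10² = 7.849 × 0.175 / 0.01 = 137.4, so 138.
- Pooled variance: [1.960 × √(2×0.10×0.90) + 0.8416 × √0.175]² / 0.10² = 140.1, so 141.
- Continuity-corrected: 159.5, so 160.
- Arcsine: effect h = 2·asin√0.15 − 2·asin√0.05 = 0.344; 2 × (2.8016/0.344)² = 132.4, so 133.
- Log odds ratio: 154.9, so 155. The log risk ratio gives 160.4, at the top of the same range.
- Fisher's exact test: about 152 (power 80.4%).

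None gives 41. The ratio 141/41 is 3.44. A one-sided test, which the plan rules out, would still need 105–130. Against 5%, a pooled two-sided n near 41 needs a control rate of about 27–28% (43 per group at 27%, 40 at 28%), and the section gives no such rate.

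**Power at the planned size, 15% versus 5%, two-sided .05.** The normal approximation with pooled variance is Φ[(0.10√n − 1.960√0.18)/√0.175]. At n = 41 this is Φ(−0.457) = 32.4%. The other rows enumerate both binomial distributions exactly.

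| Test | 41 evaluable per group | 45 evaluable per group |
|---|---|---|
| Normal approximation, pooled | 32.4% | 35.0% |
| Pearson chi-square | 35.6% | 38.6% |
| Likelihood ratio (logistic model) | 36.6% | 39.1% |
| Fisher exact | 19.3% | 23.0% |
| Wald, unadjusted logistic | 12.9% | 17.7% |

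The Wald row counts tables with a zero cell as non-significant. Such tables are not rare: at a true 5% rate, the chance of no events in the DTI arm is 0.95⁴¹ = 12% at 41 and 0.95⁴⁵ = 10% at 45.

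**Precision.** Expected 95% CI half-width for the risk difference is 1.96 × √(0.175/n): 12.8 points at n = 41 and 12.2 at n = 45, both wider than the 10-point target.

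**Pilot rates.** With 10 per subgroup, 15% is 1.5 patients and 5% is 0.5 patients. Neither is possible.

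**The case against.** The failed derivation has no good defence: the section states no other effect size, one-sided test or design feature that would reduce 141 to 41. The fair objections concern how far the point reaches.

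- **The power of the planned model is 13%.** A reader might infer this because the primary analysis is logistic regression. The Statistical Plan does not say whether the test is Wald or likelihood ratio, nor how zero cells are handled, and the likelihood ratio test from the same model has 36.6% power. About one third, lower under Fisher or Wald, is what can be said.
- **The planning rates ignore fistula, and the true event rate is 30–50%.** The endpoint does count new fistula, but the sample size section does not say that the pilot rates left it out. The Introduction's 30–50% refers to patients without a fistula, over months to years after drainage. This trial uses one-time radical resection and a 6-month endpoint, so the figure is not a planning rate. If the control rate were that high, a three-fold reduction would be easier to detect: with Pearson at 41 per group, power is 64.5% for 30% vs 10%, 80% for 40% vs 13.3% and 91% for 50% vs 16.7%. The low-power conclusion is therefore conditional on rates near 15% and 5%.
- **The attrition step should give 46.** It is true that 41/0.9 = 45.6 rounds up to 46. But this is one patient per arm on a base figure that is itself unsupported, and asking for 46 (92 in total) while keeping 90 would be inconsistent. It is not worth correcting.
- **The pilot percentages are the wrong part.** The documents do not show this. 15% and 5% equal 3/20 and 1/20, so the denominator may be what is misreported.

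**Conclusion.** The point stands. On the plan's own inputs, 41 per group is wrong by a factor of about 3.4, and so is the 80% power derived from it. At 15% versus 5%, actual power with 41 evaluable per group is 32–37% by the normal approximation, Pearson or likelihood ratio test, 19% with Fisher and 13% with Wald. With no attrition the figures are 35–39%, 23% and 18%. No choice among these tests brings power to even half of the claim.

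This rests on independent binary outcomes, 1:1 allocation, the stated rates and no covariate adjustment. The impossibility of 15% and 5% from subgroups of 10 needs no assumption. The documents do not support a claim that the trial is underpowered at every plausible event rate, because the rate under the fistula-inclusive definition is not given.

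**What to change.** In Sample Size Calculation and the registry record:

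1. Keep 90 patients and replace the 80% claim with the actual power for 15% versus 5% at 41 evaluable per group, naming the test (for example, 32% by the pooled normal approximation). Add that 80% would need about 141 evaluable per group; with 10% loss that is 141/0.9 = 156.7, so 157 per group or 314 in total.
2. Commit to reporting the recurrence difference with its 95% CI, expected half-width about 12–13 points, and state that a non-significant result will not be read as no benefit.
3. Give the pilot's true numerators and denominators, and say whether its events followed the Primary Efficacy Outcome definition, including new fistula.

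The cost is a wording amendment, which needs Ethics Committee approval and a registry update under Management of Protocol Amendments, and a much less favourable power statement. It adds no patients and changes no procedures. With 37 enrolled by January 2026 and analysis planned for the second quarter of 2027, it can be done before any outcome comparison. Enlarging the trial instead would be the sponsor's decision; correcting the claim does not require it.
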